### Study Setting

The participants for this trial will be selected from specialized peripheral camps conducted in various urban and rural areas surrounding Wardha, Maharashtra, by the Datta Meghe Institute of Higher Education and Research, Mahatma Gandhi Ayurved College Hospital and Research Centre and the *panchakarma* (a prominent Ayurvedic tool) outpatient and inpatient department of Mahatma Gandhi Ayurved College Hospital and Research Centre.

Patients of either gender aged between 20 and 60 years clinically diagnosed as per the *International Statistical Classification of Diseases, 10th Revision* criteria code 75.00 regarding primary first- and second-grade FS will be selected.

The 2013 SPIRIT (Standard Protocol Items: Recommendations for Interventional Trials) guidelines will be followed for this study.

Simple randomization will be conducted using a computer-generated table. The participant enrollment process, allocation sequence creation, and intervention assignment will be handled by the researcher.

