## Methods

### Overview

This study is an interventional, randomized, single-blind (assessor), 3–parallel arm study to compare the efficacy of honey thermal microcautery versus standard physiotherapy versus *S cordifolia* oil via nasal administration in the management of FS. We will intervene using honey thermal microcautery 2 times (the first and seventh day) along with placebo capsules twice daily for 7 days. Standard physiotherapy will be administered once a day along with placebo capsules twice daily for 7 days. *S cordifolia* oil via nasal administration will be administered via 8 drops in each nostril along with placebo capsules twice daily for 7 days. Follow-up will be conducted on the 8th, 16th, and 32nd days. Placebo capsules will be administered to reduce the psychological effect that patients might feel from knowing that they are not receiving any oral medicine, especially in the honey thermal microcautery group, where the treatment is administered only 2 times a week.

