### Objectives

This study aims to determine the comparative effectiveness of honey thermal microcautery, standard physiotherapy, and *S cordifolia* oil nasal administration in managing FS. The primary objectives are to quantify pain reduction, measured via the visual analogue scale (VAS), and assess improvements in ROM, as well as administer the McGill Pain Questionnaire and Shoulder Pain and Disability Index (SPADI) for each treatment group at specific time points: 8 days, 16 days, and 32 days after the intervention.

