#### SPADI Measurement

The pain scale and disability score will be decided based on a questionnaire administered by the researcher to the participants [30], as shown in Multimedia Appendix 1. Verbal anchors for the pain dimension are “no pain at all” and “worst pain imaginable,” and those for the functional activities are “no difficulty” and “so difficult that it required help.” The scores from both dimensions are averaged to derive a total score.

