### Randomization and Allocation

Computer-generated random numbers will be used to create a randomization chart. The participants will be randomized at a ratio of 1:1:1. To guarantee that treatment assignments are balanced, allocation sequence creation will be conducted using permuted blocks and provided in a randomized table. The researcher will enroll and give the participants an intervention and allocation sequence.

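### The role that creates the allocation sequence also enrols, assigns and administers the SPADI, so allocation is unconcealed and the assessor blind is contradicted for that outcome; the randomisation method is also stated two ways

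*Protocol article*

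**What the plan says.** **Who does what.** Study Setting states: "The participant enrollment process, allocation sequence creation, and intervention assignment will be handled by the researcher". Randomization and Allocation repeats two of the three tasks: "The researcher will enroll and give the participants an intervention and allocation sequence". Neither section separates the list from the person enrolling.

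**Who assesses.** SPADI Measurement states: "The pain scale and disability score will be decided based on a questionnaire administered by the researcher to the participants". The Objectives section places this instrument among the primary objectives: "administer the McGill Pain Questionnaire and Shoulder Pain and Disability Index (SPADI) for each treatment group at specific time points".

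**What blinding is claimed.** The Abstract and the Methods Overview call the trial single-blind, with the assessor as the blinded party. Data Collection Plan and Management goes further: apart from need in patient care, neither participants nor study personnel are to learn the allocation.

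**How patients are randomised.** Study Setting: "Simple randomization will be conducted using a computer-generated table". Randomization and Allocation: "allocation sequence creation will be conducted using permuted blocks and provided in a randomized table", at 1:1:1 and with balance as the stated purpose. The Abstract and the sample-size section fix 20 patients per group, 60 in all.

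**The concern.** Randomisation protects against selection at entry only if the person deciding on entry cannot foresee the next assignment. Here the list maker also enrols. The eligibility criteria leave room for judgement, for example on fitness for nasal oil or for cauterisation. A patient could be accepted, deferred or declined with the next arm in mind, and the resulting imbalance need not show in the recorded covariates.

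The SPADI is administered by the role that assigned the treatment, and the Discussion states in advance that microcautery is expected to do best. Any interviewer influence would therefore have a foreseeable direction, on an outcome listed as primary and used again in the Day 32 sustained-relief definition.

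Simple randomisation and permuted blocks are different procedures. While both stand, the trial report cannot state accurately how patients were allocated.

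**Working it through.** **1. Roles set side by side**

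| Task | Section | Who |
|---|---|---|
| Create sequence | Study Setting | the researcher |
| Enrol | Study Setting; Randomization and Allocation | the researcher |
| Assign | Study Setting; Randomization and Allocation | the researcher |
| Administer SPADI | SPADI Measurement | the researcher |
| Goniometer readings | Normal ROM of the Shoulder Joint | not stated |
| Collect VAS, McGill | their Outcomes subsections | not stated |

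The first three rows defeat concealment, because a list cannot be hidden from its author. The fourth contradicts the assessor blind for the SPADI. The last two rows show neither blinding nor unblinding.

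**2. How predictable is the next assignment?** For the author of the list it is fully predictable under either method. For comparison, take someone who sees only past assignments and knows the block size. The article gives no block size, so sizes of 3 to 12 are assumed:

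| Block size (assumed) | Next assignment certain | Best guess correct |
|---|---|---|
| 3 | 33% | 61% |
| 6 | 20% | 56% |
| 9 | 14% | 53% |
| 12 | 11% | 51% |

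Chance is 33%. Block size 3 can be checked by hand: the three positions are guessed correctly with probability 1/3, 1/2 and 1, which average 0.611, and one position in three is certain. The other rows are simulated. Separating the list from enrolment thus removes most of the certainty, and longer blocks remove more.

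**3. The plan's sample size.** The inputs are Z values 1.96 and 0.84, SD 0.58 and difference 0.526 (Sample Size section):

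n = 2 × (1.96 + 0.84)² × 0.58² / 0.526² = 19.06, rounded up to 20 per group.

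The stated figure is reproduced.

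**4. Does simple randomisation deliver 20 per group?**

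P(20/20/20) = 60! / (20!³ × 3⁶⁰) = (5.778 × 10²⁶) / (4.239 × 10²⁸) = 0.0136.

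At least one arm falls below 20 in the other 98.6% of trials. The smallest arm has 16 or fewer patients in 49% of trials and 15 or fewer in 32%.

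**5. What does that imbalance cost?** Pairwise power by normal approximation is Φ(0.526 / (0.58 × √(1/n₁ + 1/n₂)) − 1.96).

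- 20 v 20: Φ(2.868 − 1.96) = 81.8%.
- 15 v 22: Φ(2.708 − 1.96) = 77.3%.
- Averaged over all splits of 60 under simple randomisation: 80.5%.

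The average loss is 81.8 − 80.5 = 1.3 points. Simple randomisation does not match the fixed group sizes, but the loss of power is small.

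**The case against.** **One individual?** The text names a role. Project staff, a practitioner, a principal investigator, a coinvestigator and a statistician also appear in the article, and it never says outright that a single person makes the list, enrols and interviews. That stands as a limit. The single role is still the plain reading, and the assignment of tasks is stated affirmatively; it is not a detail left for a fuller protocol to supply.

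**Does the whole assessor blind fail?** A reader might infer this. The documents show the conflict only for the SPADI. Nobody is named for range of motion, which contains the sample-size variable (abduction) and is where a blinded assessor protects most.

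**Burn marks.** A reader might infer that whoever holds the goniometer will see them. The microcautery procedure does speak of burns, and Day 8 follows the second session by one day, so marks then are plausible. Nothing says they persist to Days 16 or 32, or that the shoulder is uncovered during measurement.

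**Imbalance as a measure of harm.** The 1.4% and 32% figures might be read as the size of the problem. They do not measure loss of concealment, and their power cost is about one point. The section devoted to randomisation specifies blocks, so this part is mainly a wording conflict.

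**Could analysis repair it?** Statistical Methods foresees analysis of covariance for age and baseline severity if needed. That partly addresses steering on recorded severity. It does not reach motivation or other unrecorded factors.

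**Patients know their procedure.** This is true, so a blinded interviewer leaves the patient-reported scores open to expectation bias. It limits what the fix achieves but does not remove the contradiction.

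**Conclusion.** The point holds in three parts.

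1. **Concealment.** As written, the enrolling role also creates the sequence, so every assignment made under that arrangement can be known beforehand. This assumes that the researcher is the same person, or shares the list, across the three tasks. It is the most serious part, because adjustment cannot reliably undo selection at entry. The resulting bias cannot be sized from the documents.
2. **Blinding.** The assessor-blind claim, and the statement that study personnel will not learn the allocation, are contradicted for the SPADI. For range of motion, VAS and McGill, unblinding is a risk that the article leaves open; it is not documented.
3. **Method.** Two incompatible randomisation methods are stated. Only permuted blocks fit the fixed 20 per group (1.4% chance of that split otherwise), at an average power cost of about 1.3 points under the plan's own difference and SD.

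The first two parts need correction for internal validity. The third needs reconciling so that the trial can be reported accurately. The sample size is unaffected.

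**What to change.** 1. **Study Setting:** delete the reference to simple randomisation and keep permuted blocks, as in Randomization and Allocation.
2. **Study Setting and Randomization and Allocation:** have the statistician foreseen in Statistical Methods, or an existing team member who neither enrols nor treats, generate and hold the list. Release each assignment only after enrolment and baseline measurements are recorded.
3. **Normal ROM of the Shoulder Joint and SPADI Measurement:** state that the SPADI interview and the range-of-motion readings are taken by an existing team member with no part in allocation or treatment. Keep the interview mode, so that the instrument does not change mid-trial. Where practicable, cover the shoulder alike in all arms during goniometry.
4. **Timing:** apply this to all patients still to be enrolled, and disclose how earlier patients were allocated and assessed. The article reports 16 recruited by January 2025, which left 60 − 16 = 44 at that date; current enrolment is unknown.

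**Cost:** a short amendment and some reassignment of tasks. The downsides are a change of assessor mid-trial and slightly harder goniometer landmarks under a cover. VAS, SPADI and McGill scores stay open to expectation bias because patients know their procedure, and the report should say so.

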### Inclusion and Exclusion Criteria

This study will include (1) patients who are willing to provide written informed consent; (2) patients who are fit for nasal oil administration as per classic Ayurvedic guidelines [21] (ie, those who are free of indigestion; have not consumed food or alcohol recently; or do not have severe thirst, hunger, or exhaustion); (3) patients of either gender aged 20 to 60 years [22]; (4) patients with controlled type 2 diabetes mellitus (fasting blood sugar ≤140 mg/dL and postprandial blood sugar ≤180 mg/dL); and (5) patients with primary FS at the inflammatory (first) and frozen (second) stages. This study will exclude patients who are unfit for thermal cauterization [23]; patients who are contraindicated for physiotherapy (eg, those with epilepsy or a pacemaker); patients with trauma or injury (eg, dislocation or fracture of the shoulder and clavicle); patients with uncontrolled hypertension (160/100 mm Hg); patients who have rheumatoid arthritis, spinal canal stenosis, all types of malignancies, and stroke; patients with infectious conditions or systemic disorders; patients who are indicated for FS surgery; postoperative patients with FS; and pregnant and lactating women.

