## Introduction

### Background

Frozen shoulder (FS) is an ailment frequently seen in general practice. The prevalence of FS, also referred to as adhesive capsulitis and periarthritis, is between 3% and 5% in the general population and up to 20% in those with diabetes. It affects people aged between 40 and 60 years more frequently, including women and manual laborers [1,2]. In patients with diabetes, the incidence is 2 to 4 times higher than in the general population [3]. The prevalence of people who experience pain in the other shoulder after the first shoulder has healed is 6% to 17%, usually within 5 years. It is slightly more likely that the nondominant shoulder will be impacted [4]. The range of motion (ROM) in all directions is significantly reduced in FS (capsular pattern). It results from swelling, scarring, thickening, and shrinking of the capsule that typically encloses the shoulder joint [5]. Global fibroplasia results from a disruption in local collagen translation in FS, which is characterized by severe inflammatory changes in the capsule that point to the involvement of inflammatory mediators (interleukins, cytokines, B and T lymphocytes, growth factors, matrix metalloproteinases, tumor necrosis factors, and fibroblast activation markers) [6-9]. Synovitis-related inflammatory response in the capsule precedes the fibrotic rigidity of the capsule in cases of FS. Using nonsteroidal anti-inflammatory drugs, steroids, physiotherapy, and occasionally hydrodilatation and surgical procedures is the first line of treatment for FS. For most patients, conservative treatment, which includes corticosteroid infiltration and physiotherapy, is considered a suitable choice [1]. Still, despite conservative care, up to 50% of patients claim to have persistent pain, and up to 60% have noticeable motion restriction [10,11].

Steroid injections offer strong anti-inflammatory effects for FS, but potential complications such as pain and glucose changes may prevent patients from accepting this method. Patients endure lengthy rehabilitation times accompanied by a significant degree of pain and everyday disabilities [12,13]. Hence, an alternative Ayurvedic therapy is required in treating FS.

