#### Primary Variable: Abduction Improvement

The primary variable, shoulder abduction improvement, was used to calculate the minimum sample size required for the study, ensuring adequate power to detect a meaningful difference between groups. The primary variable in this study is shoulder abduction improvement, measured as the increase in the range of motion after the intervention. Based on expected differences, variability, significance level, and power, the minimum sample size required was calculated to ensure reliable detection of a meaningful improvement

Where the mean score for abduction in *shudhabala taila nasya* pre=2.23 (as per the study by Revathi et al [22]).

Mom score for abduction in *shudhabala taila nasya* post at follow-up=1.06.

Difference (pretest-posttest)=1.17

SD=0.58.

Considering 45% superiority in the thermal microcautery group=(1.17) × 45 = 0.526

Mean differenсе *δ*=0.526

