### Statistical Methods

One-way ANOVA will be applied to compare the means of the 3 groups. If ANOVA indicates a significant difference, post hoc tests will be further applied (eg, the Tukey honestly significant difference test) to identify which group differs. A *P* value of <.05 will be considered statistically significant. Covariates such as age and baseline severity will be considered, and adjustments will be made using analysis of covariance if needed. The analysis will be intention to treat, with missing data handled through multiple imputation. Statistical assistance will be provided by a statistician or someone skilled in statistics. We will use SPSS (version 26; IBM Corp) for statistical analysis.

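### Disease stage, judged at entry for every patient, is used neither in the allocation nor in the planned analysis, which costs precision and leaves a chance stage imbalance uncorrected

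*Protocol article*

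**What the plan says.** All references are to the protocol article.

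- **Eligibility** (Inclusion and Exclusion Criteria): both of the first two stages are admitted, "patients with primary FS at the inflammatory (first) and frozen (second) stages". Study Setting says the same in terms of grade.
- **Relation between the stages** (Background): "Synovitis-related inflammatory response in the capsule precedes the fibrotic rigidity of the capsule in cases of FS". No section gives the course of abduction or pain by stage.
- **Allocation**: Study Setting states "Simple randomization will be conducted using a computer-generated table". Randomization and Allocation states "The participants will be randomized at a ratio of 1:1:1" and that "allocation sequence creation will be conducted using permuted blocks and provided in a randomized table". Neither section names a stratification factor.
- **Sizing variable** (Primary Variable: Abduction Improvement): "The primary variable in this study is shoulder abduction improvement, measured as the increase in the range of motion after the intervention".
- **Analysis** (Statistical Methods): "One-way ANOVA will be applied to compare the means of the 3 groups", followed by post hoc tests if significant. On covariates: "Covariates such as age and baseline severity will be considered, and adjustments will be made using analysis of covariance if needed".

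**The concern.** Stage has to be judged for each patient before entry, because it is an inclusion criterion. The information therefore exists at no extra cost, yet neither the allocation nor the stated analysis uses it.

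If inflammation comes first and capsular rigidity later, the two groups of patients may well change differently in pain and abduction over 32 days. Baseline severity, the nearest covariate named, is an imperfect stand-in, since patients in different stages can share the same pain score or abduction value.

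Two things are at stake. First, any variation between stages stays in the error term and lowers power. Second, blocks or simple randomisation balance numbers at best, not stage. In a trial with 20 per arm, meant to say which of three treatments is best, the one realised allocation may carry a stage gap that the unadjusted comparison cannot remove.

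**Working it through.** **Inputs from the article (Sample Size sections):** δ = 0.526 (45% of a pre-post change of 1.17), SD = 0.58, Zα = 1.96, Zβ = 0.84, 20 per group, 60 in total.

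**Assumptions, not in the article:** 30% or 50% of patients in one stage; a stage difference d of 0.5 or 1 SD in abduction change, in within-stage SD units.

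**1. The plan's own figure.** n = 2 × (1.96 + 0.84)² × 0.58² / 0.526² = 19.06, which supports the stated 20 per group. The sized effect is 0.526 / 0.58 = 0.91 SD. The rest is in SD units, because the sizing uses a graded score (2.23 to 1.06) while range of motion will be measured in degrees.

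**2. How often stage is imbalanced.** Random splits of 60 patients into 3 × 20, with the number in one stage fixed:

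| In one stage | Largest gap of three arms ≥20 points | Largest gap ≥25 points | One given pair ≥25 points |
|---|---|---|---|
| 30 of 60 | about 50% | about 35% | about 16% |
| 18 of 60 | about 44% | about 29% | about 12% |

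**3. How far a gap moves a contrast.** Shift = gap × d.

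- d = 1: 0.25 × 1 = 0.25 SD; 0.25 / 0.91 = 27% of the sized effect.
- d = 0.5: 0.25 × 0.5 = 0.125 SD; 0.125 / 0.91 = 14%.

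If 0.58 is the total SD including stage variation, the within-stage SD is smaller by the factor 1/√(1 + 0.25d²), and the 27% becomes about 25%.

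**4. Precision.** At a 50:50 mix, stage accounts for 0.25d² / (1 + 0.25d²) of the variance: 0.25 / 1.25 = 20% at d = 1, and 0.0625 / 1.0625 = 6% at d = 0.5.

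**5. Error rate and power of the three-arm ANOVA.** Simulated at a 50:50 mix; for power, total SD is 0.58 and one arm is shifted by 0.526.

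| Stage effect | Type I error, unadjusted, all allocations | Unadjusted, largest gap ≥25 points | Power unadjusted | Power with stage in the model |
|---|---|---|---|---|
| none | about 0.05 | about 0.05 | 0.83 | about 0.01 lower |
| 0.5 SD | 0.05 | 0.059 | 0.83 | 0.85 |
| 1 SD | 0.049 | 0.080 | about 0.83 | 0.90 |

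At 1 SD, allocations without such a gap have an error of 0.033, which is why the overall rate stays at 5%. With stage in the model, the error given an imbalance returns to about 5%.

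**The case against.** The strongest reply is that randomisation already allows for this. Chance imbalance in any prognostic factor is part of the 5% error rate, and the simulation confirms it. A 60-patient trial is not obliged to stratify. This stands: a reader might infer that the design is biased, and the documents do not support that. What remains is the loss of precision and the raised error in those allocations that turn out imbalanced.

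Second, the article does not say that abduction or pain runs a different course by stage. Background gives only an order of pathology, and it describes reduced motion in frozen shoulder generally. This also stands. A reader might infer that different natural courses are established by the article's own account; they are only made plausible, and the 0.5 to 1 SD effect is assumed.

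Third, the covariate list is illustrative, and a full list may sit in an analysis plan that is not shown. An incomplete list is indeed no defect. But the article does fix an unadjusted test as the main comparison and leaves adjustment to need, with no stated trigger. Deciding on covariates once the imbalance is visible is weaker than naming them beforehand. Baseline severity may absorb part of a stage difference, though not necessarily all of it.

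Fourth, the 35% is the largest of three gaps. A reader might apply it to a particular comparison, such as thermal microcautery against nasal oil, on which the sample size rests. For that pair the figure is about 16%.

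**Conclusion.** The point holds as a matter of efficiency and of protecting the realised comparison. Both stages are enrolled, allocation does not balance them under either description of the randomisation, and the stated analysis does not use stage. Overall type I error is unaffected.

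If stage matters by 0.5 to 1 SD, adjustment lifts power by roughly 0.02 to 0.07 and removes a shift of 14% to 27% of the sized effect in trials with a 25-point gap. If stage does not matter, almost nothing is gained and about 0.01 of power is lost. These sizes rest on an assumed stage mix and an assumed stage effect, neither of which the article supplies. The improvement is worth making because it is nearly free, not because the trial would otherwise be invalid.

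**What to change.** In Statistical Methods, replace the conditional adjustment with a prespecified model for the between-arm comparison in all 60 patients: treatment, stage (inflammatory or frozen) as a fixed factor, and the baseline value of the outcome. Record stage on the case report form from the assessment made before allocation, including for the 16 patients recruited by January 2025.

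The cost of the stage term is 1 of the 57 residual degrees of freedom, plus about 0.01 of power if stage has no effect. The baseline value takes one more degree of freedom. The sample size is unchanged.

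Stratifying the blocks by stage for patients not yet randomised (60 − 16 = 44 as of January 2025) is optional. It would mean two block lists and a change in the middle of the trial, with the first 16 relying on the model term in any case. It also first requires reconciling the simple randomisation in Study Setting with the permuted blocks in Randomization and Allocation. The model term alone deals with whatever imbalance arises.
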